## Abstract

**Background:**

Despite advances in stent design and PCI optimization, stent failure remains clinically relevant in patients with coronary artery disease. This process is primarily driven by vascular injury and maladaptive healing, leading to neointimal hyperplasia, neoatherosclerosis, and recurrent ischemic events. A subset of patients remains vulnerable despite angiographically successful PCI, reflecting residual risk not fully captured by procedural assessment alone. Novel strategies to reduce this residual risk are therefore warranted. Proprotein convertase subtilisin/kexin type 9 (PCSK9) inhibitors, beyond potent LDL-C reduction, have demonstrated plaque-stabilizing effects. Preclinical data suggest that PCSK9 promotes proinflammatory cytokine release, vascular smooth muscle cell proliferation, and impaired endothelial repair—mechanisms implicated in adverse vascular responses after PCI.

**Aim:**

To determine whether proactive, short-term evolocumab improves outcomes in patients with coronary artery disease at high residual risk after PCI.

**Methods:**

The HANYANG-PICK trial is a prospective, randomized, open-label, multicenter study enrolling patients with post-PCI _max_LCBI_4mm_ ≥200 on NIRS-IVUS. Participants will be randomized 1:1 to standard care or standard care plus evolocumab 140 mg subcutaneously within 24 h of PCI and at 2 weeks. The primary endpoint is the composite of all-cause death, myocardial infarction, stroke, or any clinically driven revascularization at 12 months.

**Ethics and dissemination:**

The protocol has been approved by the Institutional Review Board of all participating centers. Written informed consent will be obtained from all participants. Results will be disseminated in peer-reviewed journals and at scientific conferences.

**Conclusions:**

The HANYANG-PICK trial is an exploratory, hypothesis-generating randomized study designed to test whether proactive, short-term PCSK9 inhibition initiated during the early post-PCI period can reduce adverse outcomes in patients with high residual risk identified by post-PCI intravascular imaging.

**Clinical Trial Registration:**

https://clinicaltrials.gov/study/NCT07084259, Identifier NCT07084259.

## Introduction

Despite advances in stent technology, intravascular imaging, and secondary prevention, stent failure still occurs at an annual incidence of approximately 1%–2% in patients with coronary artery disease undergoing percutaneous coronary intervention (PCI) (1). This entity encompasses stent thrombosis, intimal hyperplasia, and neoatherosclerosis—pathophysiological processes driven by procedure-related vascular injury and maladaptive healing that follow balloon angioplasty and stent deployment (1–3). Notably, a subset of patients continues to experience these complications despite angiographically successful PCI, underscoring the presence of residual biological risk that is not fully captured by procedural or angiographic assessment alone. Identifying such individuals and developing strategies that target these biological pathways therefore remain important unmet clinical needs.

Proprotein convertase subtilisin/kexin type 9 (PCSK9) inhibitors, through potent LDL-C reduction, have been shown to improve clinical outcomes in patients with atherosclerotic cardiovascular disease (4–6). Beyond lipid lowering, these agents have been associated with favorable changes in plaque composition, including reductions in plaque volume and lipid burden, as well as thickening of the fibrous cap—features consistent with stabilization of vulnerable plaque (7–9). Preclinical evidence further indicates that PCSK9 is involved in proinflammatory cytokine release (10–12), vascular smooth muscle cell proliferation (13, 14), and impaired endothelial repair (15, 16), all of which may contribute to maladaptive vascular healing following PCI. Collectively, these observations suggest that PCSK9 inhibition may favorably influence vascular responses during the early post-PCI period (17–19).

We therefore hypothesize that proactive PCSK9 inhibition during the early vulnerable phase after PCI may attenuate adverse vascular responses associated with maladaptive healing and reduce subsequent cardiovascular risk in selected high-risk patients. This early post-PCI period encompasses both the acute inflammatory and subacute proliferative phases (20–23), during which plaque-related biological activity remains dynamic. To capture this biologically critical window, we selected a short-term, 4-week regimen of evolocumab, which provides sustained PCSK9 suppression with only one or two injections, thereby optimizing both adherence and feasibility within an exploratory, hypothesis-generating trial framework.

The HANYANG-PICK trial (HArnessing Near-infrared spectroscopy–intravascular ultrasound imaging for Yielding AdvaNced Guidance with a PCSK9 inhibitor for Improving Cardiovascular outcomes in high-risK patients) was designed to test this hypothesis in patients with high residual intraplaque lipid burden after PCI, defined as post-PCI _max_LCBI_4mm_ ≥ 200 on NIRS-IVUS. By using post-PCI intravascular imaging rather than angiographic or baseline lesion characteristics alone, this imaging-based risk-enrichment strategy aims to identify patients with persistently high residual risk despite technically successful revascularization. This prospective, investigator-initiated, randomized, open-label trial evaluates whether a proactive, short-term, 4-week course of evolocumab initiated immediately after PCI can favorably influence clinical outcomes by targeting a high-risk patient population during the early post-PCI period.

## Methods

### Study design and population

The HANYANG-PICK trial is a prospective, investigator-initiated, randomized, open-label, multicenter study conducted at university hospitals in Korea and the overall study design is illustrated in Figure 1. Eligible patients are aged ≥19 years with coronary artery disease, including stable angina, silent ischemia, or acute coronary syndromes, undergoing PCI with NIRS-IVUS imaging. Post-PCI _max_LCBI_4mm_ ≥200 is required for randomization. This threshold was selected to identify patients with substantial residual risk after angiographically successful PCI, as previously associated with increased adverse cardiovascular events (24, 25). Key exclusion criteria include target lesions involving in-stent restenosis (ISR), hemodynamic instability within 24 h prior to PCI, and life expectancy <1 year.

**Figure 1 F1:**
[figure not shown]
Study flow and schematic overview of the HANYANG-PICK trial design. This figure illustrates the overall study flow and design of the HANYANG-PICK trial. Patients with coronary artery disease undergoing NIRS-IVUS–guided PCI are screened immediately after PCI, and those with high residual intraplaque lipid signal defined as post-PCI _max_LCBI_4mm_ ≥200 are enrolled. Eligible patients are randomized in a 1:1 ratio to standard guideline-directed lipid-lowering therapy alone or standard therapy plus short-term evolocumab initiated within 24 h after PCI and repeated at 2 weeks. Clinical follow-up visits are scheduled at 2, 6, 12, and 48 weeks after PCI. The primary endpoint, a composite of all-cause death, myocardial infarction, stroke, or any clinically driven revascularization, is assessed at 12 months.

### Randomization and intervention

After confirming eligibility and obtaining informed consent, patients will be randomized 1:1 to the intervention or control arm. The intervention group will receive standard post-PCI care plus evolocumab 140 mg subcutaneously within 24 h of PCI and again at 2 weeks; the control group will receive standard post-PCI care alone, including high-intensity statin therapy. All patients are required to receive maximally tolerated high-intensity statin therapy, with ezetimibe added according to contemporary guideline recommendations, unless contraindicated.

### Endpoints

The primary endpoint is the composite of all-cause death, myocardial infarction, stroke, or any clinically driven revascularization at 12 months. Clinically driven revascularization is defined as repeat revascularization performed in the presence of recurrent ischemic symptoms and/or objective evidence of myocardial ischemia, including ischemic electrocardiographic changes, stress testing, or imaging findings, according to prespecified criteria. Secondary endpoints include each individual component of the primary endpoint and target lesion failure, defined as cardiac death, target vessel myocardial infarction, or clinically driven target lesion revascularization at 12 months.

### Sample size

In a previous observational cohort (25), patients with Post-PCI _max_LCBI_4mm_ ≥200 had a markedly higher 12-month incidence of major adverse cardiovascular events (MACE) compared with those with Post-PCI _max_LCBI_4mm_ <200 (15.1% vs. 2.2%), with the overall event rate in the unselected cohort being 7.5%. Given these findings, we hypothesized that proactive, short-term PCSK9 inhibition initiated immediately after PCI in patients with post-PCI _max_LCBI_4mm_ ≥200 could reduce their MACE rate toward the average level observed in the overall population (∼7.5%). Under this assumption, a total of 316 patients (158 per group) would provide 80% power to detect this difference at a two-sided *α* of 0.20, which was chosen to support signal detection and effect-size estimation in this exploratory, hypothesis-generating randomized trial. To account for an anticipated dropout rate of 10%, the target enrollment was set at 352 patients.

### Follow-Up and data collection

Patients will be followed at 2-, 6-, 12-, and 48-weeks post-PCI. At the 6-week visit, lipid profiles will be reassessed, and subsequent lipid-lowering therapy will be optimized in accordance with contemporary guideline-directed medical therapy targeting an LDL-C level <55 mg/dL; continuation or initiation of PCSK9 inhibitors is recommended when clinically indicated. At each visit, primary and secondary endpoints will be assessed and recorded. If a patient does not attend a scheduled visit, the investigator or research coordinator will promptly contact the patient by telephone to reschedule the appointment, thereby minimizing the risk of underreporting clinical events. All clinical endpoints will be adjudicated by an independent committee blinded to treatment allocation. Data will be recorded in a secure, password-protected electronic case report form.

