### Trial Status

The first patient was enrolled on July 23, 2025. Patient recruitment is planned to continue for approximately 3 years, with enrollment expected to be completed by July 2028. Final follow-up is scheduled to be completed 4 years after trial initiation.

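### Endpoints are recorded at visits that end at week 48, 29 days before the 12-month horizon at which they are defined, and the article does not reconcile the two

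*Protocol article*

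**What the plan says.** The visit schedule appears twice in the protocol article, with the same four time points:

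- Methods, Follow-Up and data collection: "Patients will be followed at 2-, 6-, 12-, and 48-weeks post-PCI".
- Figure 1 legend: "Clinical follow-up visits are scheduled at 2, 6, 12, and 48 weeks after PCI".

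Follow-Up and data collection ties endpoint capture to these visits: "At each visit, primary and secondary endpoints will be assessed and recorded". The only telephone contact described is for a missed visit, when staff "will promptly contact the patient by telephone to reschedule the appointment".

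The endpoints have a different horizon:

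- Methods, Endpoints: "The primary endpoint is the composite of all-cause death, myocardial infarction, stroke, or any clinically driven revascularization at 12 months". The Abstract agrees.
- The secondary endpoint of target lesion failure has the same horizon: "target vessel myocardial infarction, or clinically driven target lesion revascularization at 12 months".
- The Figure 1 legend, directly after listing the visits, says that the composite, ending in "or any clinically driven revascularization, is assessed at 12 months".

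Sample size uses 12-month incidence from an earlier cohort (15.1%, with a target of about 7.5%). Statistical analysis specifies Kaplan–Meier curves, a log-rank test and Cox models.

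**The concern.** Week 48 is not 12 months. If endpoints are recorded at visits and the last visit is on day 336, nothing on the published schedule establishes whether a patient was still event-free on day 365.

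Two things follow for the absolute 12-month risks:

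- **Event-free patients censored at the last visit, no later events recorded.** The Kaplan–Meier curve is essentially flat after about day 336, and the 12-month figure is really a 48-week figure.
- **Some later events recorded.** Deaths, infarctions and revascularizations can reach the site when they happen, whereas event-free status is learned only by making contact. If events are counted up to day 365 while event-free patients are censored at the visit, late events are divided by a small and shrinking risk set, and the 12-month risk is overstated.

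At stake is a 12-month estimate that cannot be read as such or set beside the 15.1% and 7.5% on which the trial was planned. For a trial meant to support effect-size estimation and the design of a later confirmatory trial, these absolute risks are a main product.

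**Working it through.** **Inputs from the protocol article.** Last visit at 48 weeks (Follow-Up and data collection; Figure 1 legend). Horizon of 12 months, taken as 365 days (Endpoints). Rates of 15.1% and 7.5%, two-sided alpha 0.20, 80% power, 158 per group, 10% dropout, 352 enrolled (Sample size).

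**1. Reproducing the stated sample size.** Pooled two-proportion formula without continuity correction, z(0.90) = 1.2816, z(0.80) = 0.8416, mean rate 0.113:

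- n per arm = [1.2816·√(2·0.113·0.887) + 0.8416·√(0.151·0.849 + 0.075·0.925)]² / (0.151 − 0.075)²
- = (0.5738 + 0.3741)² / 0.005776 = 155.6, so 156 per arm or 312 in total (stated: 316).
- Power at 158 per arm: Φ[(0.076·√158 − 0.5738)/0.4445] = Φ(0.858) = 80.5%.
- Dropout: 316/0.90 = 351.1, so 352, as stated.

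The sizing therefore reproduces, and it rests on 12-month rates.

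**2. The gap.** 48 × 7 = 336 days; 365 − 336 = 29 days; 29/365 = 7.9% of the window.

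**3. Losing the whole gap.** Assumption: constant hazard in each arm, and nothing captured after day 336. Risk to day 336 = 1 − (1 − p)^(336/365):

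- Control: 1 − 0.849^0.9205 = 13.99%
- Evolocumab: 1 − 0.925^0.9205 = 6.93%

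| | To day 365 | To day 336 |
|---|---|---|
| Risks | 15.1% vs 7.5% | 14.0% vs 6.9% |
| Expected events, 158 per arm | 158 × 0.226 = 35.7 | 158 × 0.2091 = 33.0 |
| Power, two proportions | 80.5% | 78.1% |
| Power, Schoenfeld, HR 0.476 | 82.5% | 80.2% |

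The hazard ratio is ln(0.925)/ln(0.849) = 0.476. The loss is 2.7 events (7.5% of those expected) and about 2.4 points of power. To restore 80% power at the day-336 rates by the same formula takes 169 per arm: 338 in total, and 338/0.90 = 375.6, so 376 with dropout.

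A constant hazard spreads events evenly over the year. If events cluster early after PCI, fewer fall in the last 29 days and the loss is smaller.

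**4. Does the rest of the article close the gap?** Under Trial Status, the article gives a start in July 2025, "with enrollment expected to be completed by July 2028", and final follow-up four years after initiation, about July 2029. That leaves 12 months for the last patient, so the calendar permits a 12-month assessment. The visit list still contains none.

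**The case against.** The strongest reply is that the article plainly intends a 12-month assessment. The Figure 1 legend says so, and the Trial Status dates fit it. Visit windows, a closing telephone call and the censoring rule are details that a condensed article may leave to the full protocol. Study governance and oversight also has events adjudicated from source documents and medical records, so ascertainment need not end with the visit interview. The log-rank test and Cox model do not need patients at risk on day 365, and the same schedule applies to both arms.

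Much of this stands. A reader might infer that the last 29 days are deliberately left unobserved, or that the trial cannot estimate its stated endpoint. The documents support neither reading: they state a 12-month assessment and allow time for it, and the planned comparison is only slightly affected. A reader might also expect a large distortion of the 12-month Kaplan–Meier estimate. Its size cannot be derived from the article, because it depends on visit windows and on the share of late events recorded, and neither is given.

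The reply does not remove the contradiction. The article gives a full visit list twice, ties endpoint recording to it, and then names an assessment time that no visit on the list reaches. Adjudicating from records classifies events that have been found; it does not confirm that the remaining patients were event-free on day 365.

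**Conclusion.** The point holds as an unreconciled contradiction between the visit schedule (day 336) and the endpoint horizon (12 months).

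- **Absolute 12-month risks.** Under the schedule as published, they lack support after about day 336. They are biased upward if late events are recorded while event-free patients are censored at the visit. No size can be put on that bias from the article.
- **Treatment comparison.** The effect is modest: at most about 2.7 of 35.7 expected events and 2.4 points of power (80.5% to 78.1%), assuming a constant hazard and no capture at all in the gap. Front-loaded hazards would make it smaller.

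The full protocol, which is not shown, may contain a window or closing call that settles the matter. The article would still need to agree with it.

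**What to change.** Choose one horizon and make the Abstract, the Figure 1 legend, Endpoints, and Follow-Up and data collection agree on it.

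- **Keep 12 months.** Make the final contact a 12-month contact, by telephone if need be, with a window that opens no earlier than day 365. Truncate the analysis at day 365, so that events and event-free time are counted over the same period. The sizing stands as written.
- **Or move to 48 weeks.** Redefine the primary endpoint, its components and target lesion failure at 48 weeks, and restate the sizing. Under a constant hazard this is 14.0% vs 6.9% and about 78% power with 316 evaluable patients.

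The cost is one schedule line or one call per patient, and a 12-month contact fits the stated four-year timeline, with little slack for a late window in the last patients enrolled. The change is best made before the first patients pass week 48. The first was enrolled on 23 July 2025; if PCI was on about that day, week 48 falls around 24 June 2026. Any patient already past that visit would need one additional contact to establish status at day 365.

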### Statistical analysis

Primary analyses will use the intention-to-treat population. Kaplan–Meier survival curves will be generated for time-to-event endpoints, with between-group differences assessed by log-rank test. Hazard ratios with 95% confidence intervals will be estimated using Cox proportional hazards models. Continuous variables will be compared using Student's t-test or Mann–Whitney U test, and categorical variables with chi-square or Fisher's exact test, as appropriate. Prespecified exploratory subgroup analyses, including analyses according to sex, will be performed to assess potential effect modification.

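### The named primary comparison is an unstratified, covariate-free log-rank test; pre-specifying adjustment for post-PCI maxLCBI4mm and presentation is an optional gain in precision, not the correction of an error

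*Protocol article*

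**What the plan says.** The Statistical analysis section sets an intention-to-treat primary analysis and states: "Kaplan–Meier survival curves will be generated for time-to-event endpoints, with between-group differences assessed by log-rank test". It adds Cox hazard ratios with 95% confidence intervals. No covariate or stratum is named for either, and the Cox model is not said to be unadjusted. The Randomization and intervention section gives 1:1 allocation and names no stratification factor.

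Two baseline variables matter here. The Study design and population section makes a post-PCI maxLCBI4mm of at least 200 a condition of randomisation, so the value exists for every randomised patient before treatment. The same section admits coronary disease "including stable angina, silent ischemia, or acute coronary syndromes".

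The Sample size section reports, from an earlier observational cohort, that patients at or above 200 "had a markedly higher 12-month incidence of major adverse cardiovascular events (MACE") than those below: 15.1% against 2.2%, with 7.5% overall. On 15.1% against 7.5%, it says that 316 patients "would provide 80% power to detect this difference at a two-sided *α* of 0.20".

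**The concern.** The enrichment strategy rests on maxLCBI4mm predicting events, yet the named test makes no use of how far above 200 a patient lies, nor of whether the presentation was acute. Only about 36 events are expected. If either variable predicts events within the trial, a covariate-free comparison gives up some power. It also leaves chance imbalance between arms in the point estimate. The second matters a little more here than usual, because the Sample size section gives effect-size estimation as one purpose of the trial.

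**Working it through.** **1. Inputs from the Sample size section.** Control rate p1 = 0.151, evolocumab rate p2 = 0.075, two-sided alpha 0.20 (z = 1.2816), power 80% (z = 0.8416), 158 per group.

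**2. The plan's own figure.** Pooled two-proportion formula:

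n = [z_α √(2p̄(1−p̄)) + z_β √(p1(1−p1) + p2(1−p2))]² / (p1−p2)², with p̄ = 0.113.

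n = [1.2816 × 0.4477 + 0.8416 × 0.4445]² / 0.076² = 0.8985 / 0.005776 = 155.6, so 156 per group and 312 in total, against 316 stated. Power at 158 per group is 80.5%, and 316 / 0.90 gives 352. The sample size therefore matches an unadjusted comparison and needs no adjustment to reach its stated power.

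**3. Events and marginal effect.** 316 × 0.113 = 35.7, about 36 events. The marginal hazard ratio is ln(1−0.075) / ln(1−0.151) = 0.476.

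**4. What the article says about prognostic strength.** The 15.1% against 2.2% contrast is across the cut at 200, and every randomised patient is on the same side of it. No gradient above 200 and no event rate by presentation is given. The strengths below are therefore assumptions.

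**5. Power with and without adjustment.** Simulated trials of 316 patients, 3,000 per scenario, marginal 12-month rates held at 15.1% and 7.5%, Cox Wald test at two-sided 0.20. Assumptions: a normally distributed score standing in for maxLCBI4mm, and 50% acute presentations.

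| Assumed HR per SD of score / acute vs stable | Unadjusted | Adjusted for both | Conditional HR |
|---|---|---|---|
| 1.0 / 1.0 | 82.2% | 81.9% | 0.476 |
| 1.3 / 1.5 | 80.1% | 80.3% | 0.474 |
| 1.5 / 2.0 | 80.7% | 81.2% | 0.470 |
| 2.0 / 2.0 | 80.9% | 83.1% | 0.461 |
| 2.5 / 2.5 | 81.0% | 84.5% | 0.447 |

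Simulation error is about 0.7 points. Type I error was 0.18 to 0.21 for both analyses. A separate simulation of the same two covariates gave about 0 points under weak to moderate effects and 2.5 to 4 under strong ones.

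**6. How strong might the gradient above 200 be?** The three cohort rates imply that (7.5 − 2.2) / (15.1 − 2.2) = 41% of that cohort lay at or above 200. Assume that log-hazard rises linearly with a normal score. Fitting the three rates then gives about 1.26 per SD in the whole cohort. Truncation at the 59th percentile leaves a score SD of about 0.56, so the log-hazard SD among randomised patients is about 1.26 × 0.56 = 0.71. At that value, adjusting for the score alone (5,000 replicates) gave 79.6% unadjusted and 82.8% adjusted, a paired gain of 3.1 points (standard error 0.4). If risk is instead a pure step at 200, the gradient and the gain are zero.

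**7. Chance imbalance.** With a log-hazard SD of 0.71, the between-arm difference has SD 0.71 × √(2/158) = 0.08. In about 95% of trials this moves the hazard ratio by a factor of no more than exp(1.96 × 0.08) = 1.17 either way. The standard error of the log hazard ratio with 36 events is about 2/√36 = 0.33, so imbalance is about (0.08/0.33)² = 6% of the variance.

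**The case against.** The strongest reply is that nothing here is wrong. A log-rank test without covariates is valid under 1:1 randomisation, its type I error holds, and the sample size was built for that comparison. Chance imbalance is already covered by the test's error rate and the confidence interval. All of this stands.

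A reader might infer that the plan also fixes an unadjusted hazard ratio. The article does not say so. It neither names nor rules out Cox covariates, and a condensed article commonly leaves such a list to the full protocol or the SAP. The point is therefore confined to the one test that is named.

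A reader might also infer that the trial discards a predictor already shown to be strong. The documents do not support that. The evidence is a contrast across a threshold that all randomised patients exceed, and the gradient in step 6 depends on an assumed log-linear shape.

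Lastly, adjustment is not entirely free. An adjusted Cox hazard ratio is conditional on the covariates and differs from the marginal one: 0.447 to 0.474 against 0.476 in the scenarios with prognostic covariates. Making it primary moves the primary analysis slightly away from the quantity behind the sample size. This is a fair cost, but a small one, and it is met by naming the estimand and reporting a marginal measure beside it.

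**Conclusion.** The named test leaves two available baseline variables unused, and pre-specifying adjustment for them would be a modest improvement. It is optional: the test is valid and the stated 80% power holds without it. The expected gain is about 0 to 4 points of power: essentially nothing under weak to moderate covariate effects, and 2 to 4 points only if hazard ratios reach about 2.0 to 2.5. If neither covariate is prognostic, the loss is not material (82.2% against 81.9%, within simulation error). Removing chance imbalance is likewise a minor gain in precision. The whole range rests on assumed prognostic strengths, because the article gives no gradient above 200 and no event rate by presentation. The calculations do not support reading this as a flaw that invalidates the primary result or leaves the trial underpowered.

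**What to change.** Before outcomes are known, pre-specify the following, unless the full protocol or SAP already does so:

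- Primary: a Cox model for the 12-month composite with treatment, continuous log-transformed post-PCI maxLCBI4mm, and presentation (acute coronary syndrome against stable or silent). Keep to these two covariates, given about 36 expected events.
- Supportive: the unadjusted log-rank test as now written.
- Estimand: state that the adjusted hazard ratio is conditional on the two covariates, and report a 12-month risk difference standardised over them as the marginal measure.

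A treatment-by-maxLCBI4mm interaction test is not needed for this change.

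The cost is analysis-plan wording. maxLCBI4mm is already measured for eligibility, and presentation should be known at PCI. No change to sample size or conduct follows. The one downside is a primary estimand slightly different from the one behind the sample-size calculation. Under the Trial Status section, enrolment began in July 2025 and is expected to run to July 2028, so there is still time to fix the model. An adjusted model chosen after the results are seen would carry less weight.
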